## **10.4 Adverse Event Recording**

### *10.4.1 Solicited and Unsolicited Adverse Events*

Solicited and unsolicited adverse events (AEs) will be recorded on the diary card by the parents three and six hours after injection and at bedtime each evening for 6 evenings and entered in the eCRF.

Telephone contact will be made with the parents to encourage completion of the diary cards between days 2 and 7 following vaccination. Parents will be issued with cards containing contact details and asked to contact study personnel regarding any perceived serious adverse events. Parents will be telephoned when the subject is 12 months old to collect information on the occurrence of adverse events of special interest, SAE's, new onset of chronic illnesses and associated concomitant medication use and the diagnosis of pertussis infection or other vaccine preventable disease (VPD). Reports of pertussis or other VPD infection between study visits will be confirmed by medical record review of general practitioner or hospital records. The DSMB will review all serious adverse events.

### *10.4.2 New Onset of Chronic Illness*

The new onset of chronic illness will be collected in the same manner as solicited (by diary card used following each vaccination) and unsolicited AEs (reviewed at each study visit) and recorded in the Adverse Event page of the eCRF. These events will be collected until 12 months after recruitment.

### *10.4.3 Serious Adverse Event (SAE)*

SAEs will be recorded in the relevant source document and reported in the AE and SAE layouts of the eCRF. The original SAE reporting form should remain at the study centre with the other source documentation until the close of the study.

## **10.5 Serious Adverse Event Reporting**

All SAEs MUST BE REPORTED to the Principal Investigator (PI) within 24 hours of a site becoming aware of it. Initial notification of an SAE should be made by email or mobile telephone text to the PI immediately. The SAE report with as much information regarding the event that is available at the time should be entered onto the eCRF and the PI notified (fax or email) by close of the next business day.

Each local Investigator will be responsible for reporting individual SAEs and Periodic Safety Updates (as applicable) to the relevant Ethics Committee within the specified time-line.

The Principal Investigator (or other Investigator if so delegated) will report all SAEs (regardless of the centre of origin) causally-related to the monovalent acellular pertussis vaccine to the Chairperson of the DSMB within 24 hours of being informed of the event. The DSMB will convene a DSMB meeting within 24 hours of the SAE notification, either in person or via teleconference, and then make their recommendations to the Principal Investigator.

The Investigator at each study site will report all SAEs (regardless of causality) occurring in infants who have received the monovalent acellular pertussis vaccine to GSK Biologicals, Australia within 24hrs of being informed of the event.

The Investigator at each study site will report all SAEs causally-related to the licensed vaccines to GSK Biologicals, Australia within 24hrs or being informed of the event.

Prompt notification is essential so that regulatory requirements for SAE reporting and ethical obligations to the participants involved in the study can be met. If a telephone report is initially made, it should be followed by a faxed or scanned email copy of the SAE report,

When submitting SAEs, the Investigator should not include the name or the address of the individual participant.

Prospective data collection of adverse events (AEs), including medically attended AEs and significant AEs and serious adverse events (SAEs) will be conducted in accordance with ICH Good Clinical Practice Guidelines.

## **10.6 Adverse Event Follow-up**

Every effort should be made to follow-up participants who continue to experience an AE or an SAE on completion of the study until the AE resolves or stabilises. All follow-up information (and attempted follow-up contacts) should be documented in the participant's records.

### *10.6.1 The type and duration of the follow-up of subjects after adverse events.*

If significant adverse events or contraindications to vaccination are identified, the infant will be managed at the Immunisation Adverse Event Clinics at The Children's Hospital Westmead, Women's and Children's Hospital, Adelaide, or Princess Margaret Hospital for Children or by their usual medical care provider. Significant adverse events shall include those as defined in the Immunisation Handbook or any condition requiring admission to hospital or unexpected medical attendance. Every effort will be made to follow-up subjects who continue to experience an AE or an SAE on study completion until the AE resolves or stabilizes.

## **10.7 Regulatory Requirements**

The sponsors have a legal responsibility to notify the relevant regulatory authorities about the safety of the product under clinical investigation. Prompt notification of SAEs by Investigators is essential so that legal obligations and ethical responsibilities for the safety of other study participants are met.

The Principal Investigator will report all unexpected Serious Adverse Events, causally-related to the monovalent acellular pertussis vaccine, to the Therapeutic Goods Administration (TGA) within 7 days (fatal or life-threatening events) or 15 days (for non-fatal, non-life threatening events).

The Principal Investigator will also report all unexpected or serious adverse reactions causally related to the licensed, concomitant childhood vaccines, to the TGA Office of Medicines Safety Monitoring as soon as possible.

## 10.8 IEC Reporting Requirements

The time frame within which an IEC must be notified of deaths and study product-related unexpected SAEs is stipulated by each IEC. It is the Investigator's responsibility to comply with the requirements for IEC notification.

The parents/guardians of participants will be provided with the contact details of the study team, and the local HREC for the reporting and management of all adverse events (vaccine and non-vaccine related) that may occur during the study.

## 10.9 Composition of DSMB

[name], The Children's Hospital at Westmead  
[name], National Centre for Immunisation Research and Surveillance  
[name], Royal Children's Hospital, Melbourne

The Children's Hospital at Westmead statistician will be a formal member of the DSMB.

## 11 Assessment of Efficacy

### 11.1 Specification of the efficacy parameters.

Blood samples will be taken as follows: maternal blood at birth, infant blood at 6 weeks, 10 weeks, 6 and 8 months. We believe that each of these blood samplings is important in the evaluation of antibody kinetics and comparison of the two groups in terms of presumed disease protection.

#### *11.1.1 Antibodies to pertussis:*

IgG to PT, pertactin and FHA will be measured by ELISA in maternal and infant serum samples at GSK Biologicals, Belgium, using a validated assay.

#### *11.1.2 Antibodies to other vaccine antigens:*

Antibodies to hepatitis B virus, Hib, tetanus, diphtheria, pneumococcal serotypes (all 10 serotypes if size of blood sample permits, if not then priority serotypes are 19A, 6A, 1, 5, 7F, 6B, 23F + Protein D) will be measured on sera taken at 8 months old..

#### *11.1.3 Cellular immune responses –*

Cellular immune responses will be measured on samples collected at 10 weeks and 8 months old in participants from Perth and potentially other sites, depending on recruitment. All participants will aim to have approximately 5mls of blood in total collected at visits, 1,2,3, 5 and 6. The first priority is to collect 2-3 mls of blood for antibody measurement, as detailed in 11.1.2. If an additional 2-3mls of blood is available, then it will be used for cellular immune response measurement. This blood will be collected into an equal volume of RPMI1640 supplemented with 5% pooled AB serum (for cultures with vaccine antigens), or AIM-V serum free medium supplemented with 2-mercaptoethanol ( $4 \times 10^{-5}$  M: for cultures with PHA). The following standard stimulation matrix will be employed with all samples: background control, pertussis mix (PT, FHA, PRN), tetanus toxoid (TT; 0.5Lf/ml), hepatitis B antigen (HB; 2.5ug/ml), phytohemagglutinin (PHA; 1ug/ml). TRF will be employed to quantitated cytokine proteins - IFN $\gamma$  (TH1 immunity) and IL-5 and IL-13 (TH2 immunity). Analysis will be performed at the Institute for Child Health Research, University of Western Australia.

## **12 Methods and timing for assessing, recording and analysing of efficacy parameters.**

Serological samples will be stored frozen prior to transport in batches to GSK Biologicals, Rixensart for serology measurement. The timing of laboratory analysis is to be negotiated with GSK Biologicals and depends on recruitment rate.

Results will be analysed in GSK laboratories in batches depending availability of laboratory time, this will be negotiated with GSK Biologicals.

## **13 Administrative Aspects**

### **13.1 Initiation of the study**

Study personnel at each participating centre will have an initiation visit, performed by the investigator at that site to explain their roles and responsibilities with regard to protocol adherence.

The investigational staff may not enrol any participants prior to receipt of written approval from the Ethics committee, and completion of a formal meeting conducted by sponsors /delegate to initiate the study. This meeting will include an inventory of study supplies and a detailed review of the Protocol and source documentation including participant diary cards.

### **13.2 Monitoring of the study**

The principal investigator will arrange for a suitable qualified Monitor to monitor the study, at regular intervals, at each of the participating centres.

### **13.3 Protocol Deviation / Violations**

All instances where the requirements of the Study Protocol were not complied with will be captured in the relevant source documentation and the Study Monitor will prepare a Protocol Deviation / Violation Log. Corresponding participants may be withdrawn from the study at the discretion of the Investigator. An amendment must be agreed upon by the investigators, but not implemented until written Ethics Committee approval is obtained, except where necessary to eliminate an immediate hazard to study participants or when the change(s) involves only logistical or administrative aspects.

Study Protocol deviations/violations can be defined as follows:

- *Protocol Deviations* arise when participants who have been entered in the Study deviate from the Ethics Committee-approved Study Protocol. For example, a blood sample is not drawn at an interval specified by the Study Protocol.
- *Protocol Violations* arise when participants who did not meet the Inclusion Criteria, or who met Exclusion Criteria are entered into the study.

If a study protocol violation occurs, the Investigator must notify the appropriate Ethics Committee as soon as possible or as per local requirements. Protocol deviations will be noted in the source documentation. All study protocol deviations / violations must be noted in a Protocol Deviation / Violation Log to be maintained in the Investigator's study file at each participating centre.

## 13.4 Confidentiality

The investigators will preserve the confidentiality of participants taking part in the study. In the event that names inadvertently appear on study documentation, this information will not be processed. Participant medical records pertaining to the study may be inspected / audited at any time by authorised representatives of the sponsors, a regulatory authority or by the Ethics Committee. All records accessed will be strictly confidential. Consent to participate in the study includes consent to these inspections / audits.

## 14 Statistics

All efficacy analyses will be undertaken using the Full Analysis Set comprising all randomized participants. The safety analyses will be undertaken using the Safety Analysis Set comprising all randomized participants that receive at least one vaccination.

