## **2.4 Description of and justification for the route of administration, dosage, dosage regimen and treatment period(s).**

### *Rationale For Study Design And Key Questions From Our Pilot Study:*

#### *2.4.1 Concomitant antigen responses:*

Other vaccine antigens co-administered with Pa-containing vaccines include diphtheria, tetanus, polio, Hepatitis B and *Haemophilus influenzae* type b (Hib). In the German study, attainment of Hib antibody responses indicating protection (>0.15ug/ml) was significantly lower after the first 3 doses (88% vs. 98%). Reduced Hib immunogenicity has been associated with DTPa-Hib combination vaccines, but has only emerged as a clinical problem in the UK prior to that country introducing a Hib booster. In Australia, a Hib booster has always been routine.

There was no significant difference in response to other antigens. In our pilot study, hepatitis B antibody levels were non-significantly lower in the birth Pa group, but all participants were above the accepted threshold for protection (>10mIU/L). This study will examine IgG responses to D, T, Hib and hepatitis B post primary immunisation.

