## 3.2 HYPOTHESES

1. IgG antibody responses to pertussis toxin (PT) and pertactin (PRN) in infants receiving monovalent acellular pertussis vaccine (Pa) at birth and routine vaccines at 6 weeks are significantly higher than in unvaccinated infants by 10 weeks of age, and remain higher at 6 and 8 months of age
2. Cell-mediated immune responses to PT and PRN at 10 weeks and 8 months of age in infants receiving monovalent acellular pertussis vaccine at birth and routine vaccines at 6 weeks do not differ significantly from those in infants with first doses at 6 weeks.
3. IgG antibody responses to **PT and PRN** at each time point in infants of mothers vaccinated with dTpa within the previous 5 years do not differ significantly from infants of unvaccinated mothers.
4. In infants receiving Pa at birth and routine vaccines at 6 weeks, the prevalence of antibody levels consistent with protection to **other vaccine antigens** is not significantly reduced
5. The frequency, duration and intensity of solicited symptoms in the 6 days following vaccination and unsolicited symptoms until the next vaccination visit (up to 8 months old) will not differ significantly between the infants receiving Pa vaccine at birth and controls.

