## **6.3 Subject withdrawal criteria (i.e. terminating investigational product treatment/trial treatment) and procedures specifying:**

*6.3.1 When and how to withdraw subjects from the trial/ investigational product treatment.* Participants may withdraw from the study at any time at the request of their parent / guardian, or they may be withdrawn at any time at the discretion of the Investigator for safety, behavioural or administrative reasons.

If a subject develops any of the following then he/she will be withdrawn from the trial

- Contraindications to vaccination as listed in the NHMRC Australian Immunisation Handbook 9th Edition.
- Serious chronic illness following discussion between investigators at all sites

This will be checked at each visit. If any become applicable during the relevant study period, the subject will not be required to continue the study.

Similarly, the data will not be eliminated from analysis (intention to treat approach) if any of the following occur, however in this case the subject will continue in the study:

- Use of any investigational or non-registered drug or vaccine during the study period.
- Administration of a vaccine not foreseen by the study protocol during the period starting from 30 days before any dose of vaccine(s) and ending 30 days after.
- Administration of immunoglobulins and/or any blood products during the study period.
- Administration of immunosuppressants or other immune-modifying drugs during the study period.
- Diagnosis or suspicion of an immunosuppressive condition during the study period.

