### **14.5 Procedure for accounting for missing, unused and spurious data.**

From an analysis perspective, a 'drop-out' will be any subject who did not attend the concluding visit. A participant, who returns for the concluding visit in the protocol, even if not all prior visits were attended, is deemed to have completed the study.

Methods for imputing missing values (e.g. last post-baseline observation carried forward) or analysis models that accommodate missing data (e.g. repeated measures mixed-models) will be employed where necessary to ensure as many subjects as possible from the Full Analysis Set contribute to the efficacy analyses.

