### **14.6 The selection of subjects to be included in the analyses**

The Full Analysis Set will comprise all randomized participants. The Safety Analysis Set will comprise all randomized participants that receive at least one vaccination

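### Fixing every efficacy analysis to all randomised infants suits the week-10 superiority test, but for Hypotheses 2 and 4 it dilutes a true loss modestly towards 'no difference'

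*Protocol*

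**What the plan says.** Section 14 opens with the rule "All efficacy analyses will be undertaken using the Full Analysis Set comprising all randomized participants", and section 14.6 repeats the definition: "The Full Analysis Set will comprise all randomized participants". The only other set named is the Safety Analysis Set. Section 11.1 lists antibodies to other vaccine antigens and cellular responses among the efficacy parameters, so both fall under this rule.

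Section 6.3.1 lists events after which an infant stays in the study and in the analysis: "Similarly, the data will not be eliminated from analysis (intention to treat approach) if any of the following occur". The list includes "Administration of immunoglobulins and/or any blood products during the study period", as well as unplanned vaccines and immune-modifying drugs. Section 14.5 adds imputation or suitable models "to ensure as many subjects as possible from the Full Analysis Set contribute to the efficacy analyses".

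Section 3.2 states Hypothesis 4 as "the prevalence of antibody levels consistent with protection to" other antigens "is not significantly reduced" in birth-dose infants. Hypothesis 2 is likewise worded as no significant difference in cell-mediated responses. Section 14.1 analyses the month-8 antibody thresholds by the same approaches as the primary endpoint, which means a chi-square test first. It sets no margin and names no separate population.

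**The concern.** Under a superiority hypothesis, keeping infants who did not follow their allocation is conservative, because dilution works against the claim. Under a hypothesis of no difference, dilution works for it. A birth-group infant who never received the birth pertussis dose has in effect followed the control schedule. The more such infants there are, the smaller any true interference appears.

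The protocol itself gives reason to look for interference. Section 2.4.1 reports from an earlier birth-dose study that protective Hib attainment "was significantly lower after the first 3 doses (88% vs. 98" per cent). Section 2.4.4 reports a TH2 shift in the pilot and calls T-cell profiling essential. If the trial reports that other antigens and cellular responses are unaffected, that reassurance should not rest partly on infants who were not exposed.

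Passively acquired IgG is a second, smaller route. An infant given immunoglobulin could sit above an antibody threshold without having responded to vaccine. This bears only on the antibody endpoints. The cellular endpoints in section 11.1.3 are cytokines from stimulated cells.

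**Working it through.** **Inputs from the protocol.** 220 per randomised group and 10% dropout (Table 2 of section 8; section 14.2.1); two-sided alpha 0.05 (section 14.3); chi-square test (section 14.1); Hib above threshold 98% v 88% (section 2.4.1), read as comparison v birth dose.

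**Assumption.** f is the share of birth-group infants without the birth dose. The protocol gives no figure, so 0 to 20% is shown.

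**Step 1: the plan's own sample size.** Take 30% v 18% susceptible, the middle of the stated control range (70% with antibody), so the mean proportion is 0.24:

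n = [1.96·√(2·0.24·0.76) + 0.8416·√(0.30·0.70 + 0.18·0.82)]² / 0.12² = (1.1838 + 0.5033)² / 0.0144 = 197.7, rounded up to 198.

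198/0.9 = 220 per group. The stated size reproduces and is not in dispute. The evaluable number used below is 220 × 0.9 = 198.

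**Step 2: dilution.** Birth-group proportion p_B = 0.88(1 − f) + 0.98f, so the apparent loss is d = 0.10(1 − f).

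**Step 3: chance of a non-significant test.** P = 1 − Φ[(d − 1.96·SE0)/SE1]. SE0 is the pooled standard error and SE1 the unpooled one. The Full Analysis Set has 198 in each group. Removing the infants without the birth dose leaves 198(1 − f) in the birth group, at 88%.

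| f | Full set: loss (points) | SE0 | SE1 | P(non-sig.) | Infants removed: SE0 | SE1 | P(non-sig.) |
|---|---|---|---|---|---|---|---|
| 0 | 10.0 | 0.02564 | 0.02515 | 2.4% | 0.02564 | 0.02515 | 2.4% |
| 5% | 9.5 | 0.02521 | 0.02476 | 3.3% | 0.02576 | 0.02570 | 2.7% |
| 10% | 9.0 | 0.02478 | 0.02436 | 4.4% | 0.02588 | 0.02630 | 3.0% |
| 20% | 8.0 | 0.02387 | 0.02353 | 7.9% | 0.02617 | 0.02767 | 3.9% |

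For example, at f = 10% in the full set: (0.090 − 1.96 × 0.02478)/0.02436 = 1.70, which gives 4.4%. Removing these infants lowers the risk by 0.6, 1.4 and 4.0 percentage points at f = 5%, 10% and 20%.

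**Step 4: immunoglobulin.** Assume 2% of both groups receive it and all are lifted above threshold. Control: 0.98 × 0.98 + 0.02 = 98.04%. Birth group: 0.88 × 0.98 + 0.02 = 88.24%. The difference moves from 10.0 to 9.8 points, and the chance of a non-significant test from 2.4% to 2.7%.

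**Step 5: a smaller true loss.** With an assumed 95% v 90%, the test is non-significant 52.8% of the time at full adherence. At f = 10% it is 59.3% in the full set and 54.2% with the infants removed. Here the weight lies in reading non-significance as no reduction, not in the choice of set.

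No comparable calculation is given for cell-mediated immunity. The direction of the dilution is the same, but the protocol gives no expected group difference to dilute.

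**The case against.** The strongest reply is that the exposure at issue is one injection at the first visit. It is given by the study team, and randomisation and vaccination must both fall within 120 hours of birth. Missed birth doses may be rare, and nothing in the protocol supports any particular rate. Prior or planned immunoglobulin and blood products are exclusions (section 6.1.2), so only unplanned use in healthy infants remains, and it can occur in either group. Section 13.3 lets the investigator withdraw infants with deviations. A supportive per-protocol set is often left to the analysis plan, which is not at hand, and exclusions made after randomisation lose its protection. All of this stands, and it is why the effect is called modest.

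It does not remove the point. Sections 14 and 14.6 are not silent: they assign every efficacy analysis to one set and set no further condition for a no-difference claim.

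A reader might infer more than the documents support:

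- **That Hypothesis 3 is affected in the same way.** It compares infants by maternal vaccination status, so a missed birth dose does not mix its groups.
- **That missed or late doses at 6 weeks, 4 or 6 months merge the arms.** Both groups have the same vaccines then, so such deviations have no fixed effect on the difference.
- **That infants with missing bleeds dilute Hypothesis 4.** Those antibodies are measured only at 8 months, so there is no earlier value to carry forward.
- **That a non-inferiority error rate applies.** With an assumed 10-point margin and a true loss from 98% to 88%, the false-claim rate would be 2.5%, 3.9% and 6.1% at f = 0, 5% and 10%. The protocol plans no such test and states no margin.

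**Conclusion.** The point holds for Hypotheses 4 and 2 and for no others. The Full Analysis Set is right for the week-10 superiority test. As the only stated set for the no-reduction and no-difference claims, it leans towards the hoped-for answer.

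For a Hib loss of the size the protocol cites, the risk of missing it is 3.3% rather than 2.7% at an assumed 5% without the birth dose, and 4.4% rather than 3.0% at 10%. It becomes appreciable only at higher rates (7.9% v 3.9% at 20%). These figures rest on the assumed f, on 198 evaluable infants per group, and on infants without the birth dose responding exactly as controls. Passive antibody is probably a very small contributor.

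It would be too strong to conclude that a per-protocol set makes a 'no interference' finding safe. With 95% v 90%, more than half of trials would be non-significant whichever set is used. Judging these hypotheses by confidence intervals is the larger need, and this change does not replace it.

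**What to change.** Keep the Full Analysis Set for the primary test. In sections 14 and 14.6, add a per-protocol immunogenicity set defined separately for each bleed:

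- assigned doses received up to that bleed;
- bleed within its stated interval;
- no immunoglobulin, blood product or immunosuppressant before that bleed.

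Report Hypotheses 2 and 4 in both sets, and claim no difference or no reduction only if both agree. Present the confidence interval for each difference in both sets, so that the conclusion does not hang on a non-significant p-value. If the analysis plan already holds such a set, the protocol wording needs only to be aligned with it.

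The data are already collected: doses and dates under section 9, deviations under section 13.3. The cost is one more run of the secondary tables. The downside is a slightly smaller set that randomisation does not fully protect, which is why it should stand beside the Full Analysis Set and not replace it.
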